**Figure 1 figure1:**
[figure not shown]
Experimental design. Participants will perform the protocol twice. Prednisolone (GC), or placebo (Pla) orally in a double-blind, randomized, cross-over design. The two experimental days will be separated by 1 to 3 weeks. The -24 hour biopsy will be obtained only once, prior to the first treatment. We will use the data from this biopsy for comparison across the 2 trial days.

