### Sample Size and Data Analysis

The sample size is based on our previous work where exercise significantly increased ucOC by approximately 6.5% and insulin sensitivity by approximately 35% during a euglycaemic-hyperinsulinaemic clamp (n=11) [7,12]. As such, we estimate that the sample size needed in this cross-over design (power of 80%, alpha=0.05) is 12 individuals.

Descriptive statistics will be used to describe the volunteers’ characteristics as well as the study measurements. Changes from pre-to-post exercise within each trial and between trials will be analyzed by paired *t*-tests. General linear model analysis of the variance will be use to compare multiple time-points within and between interventions. Multilinear regression model will be used to determine associations between selected measurements. All data will be reported as mean ± standard error of mean and all statistical analyses will be conducted at the 95% level of significance ( *P*≤.05).

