### Intervention

Volunteers will attend our laboratory twice for the experimental trials (Figure 1). On the day prior to the first trial, participants will be asked to record their daily diet in a food diary, which will then be replicated the day prior to their second trial. The two trials (prednisolone or placebo) will be performed 1 to 3 weeks apart. This ensures that the effect of the single dose of prednisolone is “washed out” [25]. Twenty-four hours prior to the first trial day, and a minimum of 1 week after the VO_2peak_test, a single muscle biopsy and 15 ml of blood will be obtained. To avoid an additional biopsy, data from this resting biopsy will be used as the “24 hour prior” time-point for both the placebo and prednisolone trials. Then, at 7 PM (12 hours before the trial) on the day prior to each experimental trial participants will ingest a 20-mg capsule of prednisolone or placebo orally (Avicel- microcrystalline Cellulose NF PH105) (Figure 1).

The timing of the prednisolone ingestion is based on previously published data on the suppressive effect of acute GC treatment on osteocalcin [20]. The prednisolone dose that will be used in this study is slightly higher compared with the dose used by Nielsen et al [20] (10 mg), but is lower compared with doses used in clinical practice to treat inflammatory conditions (30-70 mg/day). Both the prednisolone and placebo will be purchased from the same pharmacy and look and taste identical. Avicel is widely used as a placebo in a variety of drug trials [26].

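### One biopsy taken before the first trial serves as the 24-hour-prior point of both trials, so second-trial changes from it can mix a period shift with a 24-hour effect

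*Protocol article*

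**What the plan says.** Under Intervention, the protocol article gives the reason for the reuse (sparing the participant a biopsy) and then fixes it: "data from this resting biopsy will be used as the “24 hour prior” time-point for both the placebo and prednisolone trials". The Figure 1 legend confirms the timing, "The -24 hour biopsy will be obtained only once, prior to the first treatment", the reuse, "We will use the data from this biopsy for comparison across the 2 trial days", and the spacing of the trials, "The two experimental days will be separated by 1 to 3 weeks".

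Intervention also lists the biopsies by session. The first session has four: -24 h, baseline, and before and after the clamp. The second has three: baseline, and before and after the clamp. The biopsy called baseline is the trial-day resting sample, taken in both sessions about 12 hours after the 7 PM capsule. It is distinct from the -24 h sample.

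Under Sample Size and Data Analysis, the model for the time course is described in one sentence: "General linear model analysis of the variance will be use to compare multiple time-points within and between interventions". The paired t-tests in that section are for changes from before to after exercise. The limitations in the Discussion do not mention the reuse.

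**The concern.** The -24 h biopsy is the only muscle sample taken before any capsule. A change from it to the trial-day resting sample is the natural within-trial reading of what the capsule alone did to Gilz, Fkbp5 and the inflammation and atrophy markers. The Introduction predicts that the protein levels of the glucocorticoid targets will not change in this time frame and that markers of muscle damage will not rise. The Discussion relies on these measurements to address its main limitation, that glucocorticoids act on tissues other than bone.

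In the second trial, that change spans the first trial as well as the capsule. Repeat biopsies of the same muscle and a bout of high-intensity exercise could plausibly shift inflammation and atrophy markers. The washout statement concerns the prednisolone dose only. A shift could then appear as a within-trial effect of prednisolone or placebo, or could hide a real change of opposite sign.

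Separately, if one value is entered at -24 h for both treatments, the two curves must start at the same point. A reader of the figure could take that for demonstrated comparability.

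**Working it through.** **Inputs from the protocol.** One -24 h biopsy, before the first treatment (Figure 1 legend). Trials 1 to 3 weeks apart, that is 7 to 21 days (Intervention; Figure 1 legend). Four biopsies in the first session and three in the second (Intervention). n = 12 and alpha = 0.05 (Sample Size and Data Analysis). Treatment order randomised in blocks (Randomization and Blinding).

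**Reproducing the stated count.** 1 + 3 × 2 = 7, which equals 4 + 3. The total of seven biopsies is consistent with a single -24 h sample.

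**Age of the sample.** First trial: 1 day. Second trial: 7 + 1 = 8 days to 21 + 1 = 22 days.

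**Effect on change scores.** Let B be the -24 h value, P and Q the trial-day resting values under prednisolone and placebo, and s the shift in the resting marker between the trials. The size of s is an assumption.

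- First-trial change from -24 h: drug effect only.
- Second-trial change from -24 h: drug effect + s.
- Mean change for each treatment with a 6:6 order: drug effect + s/2. For example, with a true prednisolone effect of 1.00, a placebo effect of 0 and s = 0.5, the means are 1.25 and 0.25.
- Prednisolone minus placebo: (P − B) − (Q − B) = P − Q. B cancels. With 6:6 order s cancels too, and the difference is 1.25 − 0.25 = 1.00.
- With 7:5 or 8:4 order, (7 − 5)/12 = 1/6 or (8 − 4)/12 = 1/3 of s remains in magnitude unless period is modelled. This is an ordinary period effect and is not caused by the shared biopsy.
- Treatment difference at the -24 h time level: B − B = 0 for every participant, with zero variance.

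**False-positive rates by simulation.** n = 12, 6:6 order, change-score SD of 1, no true drug effect, two-sided 5% test. The within-trial test is a one-sample t-test on the 12 changes from -24 h to rest, with s added to six of them. The paired test is prednisolone minus placebo at rest, without a period term.

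| Assumed s (SD) | Within-trial, -24 h to rest | Paired difference at rest |
|---|---|---|
| 0 | 5% | 5% |
| 0.25 | 7% | 4.4% |
| 0.5 | 11% | 2.9% |
| 0.75 | 18% | 1.6% |
| 1.0 | 27% | 0.7% |

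The within-trial test is inflated because its mean moves by s/2. The paired test is conservative because s enters with opposite sign in the two orders: it cancels from the mean but adds to the variance. A period term averages the two order-specific mean differences and uses the within-order variance, which does not contain s, so the 5% level and the lost efficiency are recovered. An omnibus treatment-by-time test with the duplicated -24 h cell stayed at 5% to 6%.

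**The case against.** The strongest defence is that the trial is a randomised cross-over with a placebo trial and a fresh resting biopsy on each trial day. Any drift reaches both treatments, and the Introduction frames the muscle comparison as biopsies with and without prednisolone, which is a between-treatment contrast. All of this stands. A reader might infer from the reuse that the prednisolone effect itself is biased, or that the trial's main conclusions are at risk. The documents do not support that: the shared value cancels, and the paired test without a period term becomes conservative, not inflated.

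It is also fair that no section names a one-sample test from -24 h to rest. It is one contrast that the general linear model permits within an intervention, and the terms of that model are not given and could include period. The documents establish an interval, not a shift. Some sources of drift are controlled: 48 hours without exercise and 24 hours without alcohol or caffeine before trial days, a replicated diet, an overnight fast and at least a week between trials.

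Finally, the reuse is disclosed and has a good reason in a study with seven biopsies. That answers any suggestion of concealment and justifies not taking another sample. It does not make the 24-hour label true for the second trial, nor does it justify entering the value as a time level there. Both uses are fixed in the text, so they are not details left to an analysis plan.

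**Conclusion.** The point holds for within-trial changes from the -24 h biopsy in secondary muscle markers, and for the apparent equality of the treatments at -24 h. The 8 to 22 day age of the second-trial value is exact arithmetic from the protocol. The 7% to 27% false-positive range is conditional on an assumed drift of 0.25 to 1.0 SD, a 6:6 order and a within-trial test that the protocol allows but does not name. At the low end of that range the inflation is slight.

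Not affected are the primary outcomes under Outcomes Measurements (serum ucOC and clamp insulin sensitivity), changes from the trial-day baseline biopsy and, with balanced order, the prednisolone-placebo contrast. A reader might also assume that the 15 ml blood sample drawn at the same visit is reused. The reuse statements concern the biopsy only, so that inference has no support in the text.

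**What to change.** 1. Enter the -24 h value once per participant, as a common pre-treatment observation, and not as a time level of both trials.
2. Test the resting drug effect on muscle markers as the paired prednisolone-placebo difference at the 7 AM biopsy, with a period term.
3. Report any change from -24 h to rest from a model with period, or from first-period data labelled as such.
4. In the text and Figure 1, do not call the value 24 hours prior for the second trial. State its actual age of 8 to 22 days, and note that the treatments coincide there by construction.

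The cost is analysis and figure wording, with no further biopsy. The downside is precision for the -24 h-to-rest change per treatment. With first-period data only, it rests on about six participants, and an effect of 0.89 SD, which has 80% power with 12, would have about 42%. The paired comparison at 7 AM keeps all 12 and should carry the inference.

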### Analysis

Total serum OC will be measured using an automated immunoassay. Serum ucOC will be measured by the same immunoassay after adsorption of carboxylated OC on 5 mg/mL hydroxyl-apatite slurry, following the method described by Gundberg et al [30]. β-isomerized C-terminal telopeptides (a bone resorption marker) and P1NP (a bone formation marker) will be analyzed at Austin pathology.

Muscle insulin signaling proteins, markers of muscle inflammation and atrophy signaling proteins (see below for details) will be measured by PCR and immunoblotting. Glucocorticoid signaling in muscle will be also monitored by quantitative reverse-transcription PCR analysis of glucocorticoid-target genes, *Gilz*and *Fkbp5*. Protein expression of the GILZ and Fkbp5 will also be analyzed by immunoblotting. Muscle mitochondrial respiration will be measured using Oxygraph O2k, to assess the effects of prednisolone and exercise on mitochondrial function.

### Safety Consideration

This is an invasive study that includes seven muscle biopsies (in total), two insulin clamps, blood sampling, high intensity exercise, and administration of a single dose of prednisolone. To reduce the risk associated with the study, only healthy young individuals will participate. In addition, only those who meet the inclusion criteria (as described above) will participate. During the initial graded exercise test participants will be monitored via a 12-lead electrocardiogram (ECG) to identify cardiac abnormalities that may exclude them from the study. A 12-lead ECG will also be used during the insulin clamps. Participants will be asked to report side effects associated with the administration of prednisolone (and placebo). In case of an adverse response/event the participant will be seen by the medical practitioner involved in the study. All the participants will receive a copy of their results (blood tests, body composition, and aerobic fitness).

### Ethical Considerations

This study was approved by Victoria University Human Research Ethics Committee (Application ID: HRE14-099). The trial has been regis­tered in the Australian New Zealand Clinical Trials Registry [ANZCTR, ID ACTRN12610000943044]. The investigator, regardless of the outcome, will publish the results of the study.

### Outcomes Measurements

Primary outcomes are changes in serum ucOC and changes in insulin sensitivity (glucose infusion rate per unit of insulin). Secondary outcomes are measures of skeletal muscle insulin signaling proteins for total and phosphorylated forms of protein kinase B, Akt substrate of 160 kDa, and Insulin receptor substrate 1 and 2, mitochondria function and markers of muscle inflammation including interleukin-6, tumor necrosis factor-alpha, monocyte chemotactic protein 1, interleukin 1 beta, atrogin, signal transducer and activator of transcription 3, nuclear factor kappa-light-chain-enhancer of activated B cells, forkhead box protein O1, and Muscle RING-finger protein-1. In addition, glucocorticoid-target genes, *gilz*and *Fkbp5*will be measured. G protein-coupled receptor class C group 6 member A will also be measured as it is the likely receptor for ucOC in skeletal muscle. In blood, changes in bone remodeling markers include total osteocalcin, P1NP, and beta-isomerized C-terminal telopeptides.

## Discussion

### Principal Findings

In mice, ucOC is a modulator of insulin sensitivity and ucOC treatment reduces the risk for type 2 diabetes [2,3]. In humans, data are supportive but are based on cross-sectional studies. If this study shows that suppression of ucOC with a single dose of prednisolone leads to suppression of insulin sensitivity post exercise, this suggests that ucOC is likely to participate in the modulation of insulin sensitivity in humans.

Insulin resistance is characterized by impaired insulin action in insulin target tissues. However, muscle glucose uptake is normal during and following exercise in patients with type 2 diabetes [31,32]. As such, understanding the mechanism/s behind the insulin sensitizing effect of exercise on muscle and whole-body glucose uptake can open the door for new therapeutic treatments for T2DM. In this study we focus on ucOC as acute exercise increases ucOC and higher ucOC correlate with an improvement in insulin sensitivity and glycemic control after exercise in obese men [7,12,13].

A single dose (10 mg) of prednisone suppresses OC and ucOC, an effect that lasts for at least 12 hours [20]. We hypothesize that prednisolone will attenuate the increase in ucOC in response to exercise and that this will coincide with reduced insulin sensitivity compared with placebo. This design will enable us to examine whether changes in ucOC levels are related to changes in insulin sensitivity in young healthy men. We also aim to determine the fraction of the observed reduction in insulin sensitivity that is modulated by ucOC in humans.

A potential limitation of the current study is that GC are known to effect several other organs/tissues and not only osteoblasts. As such, it is plausible that a reduction in insulin sensitivity following acute GC treatment may not be entirely due to the reduction in ucOC. However, in mice the reduction in ucOC and insulin sensitivity occurred prior to the GC-induced effects in muscle, liver, and adipose following short-term GC treatment suggesting that the changes in insulin sensitivity are related to the reduction in ucOC levels and not to the GC effects on skeletal muscle, fat, or liver [17]. Nevertheless, in the current study we will be able to identify if acute GC treatment has immediate effects on GC-target genes ( *gilz, Fkbp5*, fatty acid binding protein 4, hydroxysteroid (11-Beta) dehydrogenase 1, peroxisome proliferator-activated receptor gamma, and CCAAT/enhancer-binding protein alpha), and any detrimental effect on skeletal muscle, as markers of muscle atrophy and degradation will also be measured.

Another limitation is that the current study will investigate young, healthy men rather than patients with T2DM. As such, it will not be possible to generalize the results to this population. Follow-up studies will be required to confirm that changes in ucOC following interventions are related to changes in insulin sensitivity in patients with T2DM.

### Conclusions

Current evidence connecting ucOC to insulin sensitivity in humans is supportive, but driven by cross-sectional studies. The current dynamic study will add important knowledge concerning the role of ucOC in insulin sensitivity in humans post exercise. The project is relevant to understanding pathway/s involved in exercise-induced insulin sensitivity and the potential for using osteoblast altering drugs as a target to improve insulin sensitivity in diseases like diabetes and obesity.

## Abbreviations

DXA: dual-energy x-ray absorptiometry
ECG: electrocardiogram
Fkbp5: FK506-binding protein 5
GC: glucocorticoid
Gilz: glucocorticoid-induced leucine zipper
GIR: glucose infusion rate
P1NP: procollagen 1 N-terminal propeptide
PCR: polymerase chain reaction
T2DM: type 2 diabetes mellitus
ucOC: undercarboxylated osteocalcin
